### Bio–specimen storage and security

**Administration.** The principal investigators of the three sites are responsible for the implementation and management of the study. These principal investigators will be responsible for maintenance of optimal quality of the biological samples and will lead all analyses to be conducted as part of the study. They have, in consultation with governmental agencies and ministries of health, academia and key stakeholders, constituted a governance council to take over the management of the biobanks after the main AMANHI analyses are completed. These governing councils will meet at agreed times and at various frequencies to receive, review and approve protocols for studies that require the use of the AMANHI biological samples in the biobank.

**Temperature maintenance.** Maintenance of optimal storage temperature of all biological samples is a key issue in the biobanks and is a core component of the common protocols being used across sites. There are minor site–specific adaptations; for instance, in Karachi and Pemba, to minimise the travel distance between the families and the biobank, field laboratories have been set up and samples are transited through shuttle freezers (also maintained at between –76°C to –86°C) to the Biobank. Temperature logs are maintained for shuttle freezers during transport and main freezers at the biobank.

**Power supply and alert systems.** Availability of reliable power supply is cited as one of the reasons why biobanking may not be feasible in LMICs and so premium was placed on this [25]. All sites have therefore procured additional power back–up generators as well as high capacity uninterruptible power supply (UPS) systems to protect sensitive equipment from power trips, surges and fluctuations. For instance, the Pemba site has installed a 18KV solar power system with 2 days autonomy as one of the power backup system other than national grid and generators. The biobanks have also been fitted with security alarm systems that immediately report through text messages and emails (to the principal investigators and appropriate technical persons for immediate redress) any temperature fluctuations and power trips irrespective of whether the back–up systems are activated. All these have been piloted and are being closely monitored.

**AMANHI Biobanking software.** A special Windows–based software has been developed for the capture of the AMANHI biospecimen collection. This software which was developed by the Pemba team is aimed first at reducing transcription errors in the data capture and to align the sample collection process with the common protocol. It has in–built range and consistency checks and will only accept data appropriate for the field in which it is being entered. All samples and study materials are provided labels with encrypted 2D digital signature codes that are read by a 2D scanner into the software. The software has undergone several rounds of testing before deployment to all the sites for use. Training has been provided to all the sites on the installation and the use of the software for data capture and real–time troubleshooting is being done for all sites because individual sites do not have the facility to edit the database. In case of any errors they have to inform the WHO coordinator for the study (Leader, MCA/MRD, Newborn Health Research) who has the password. A specified software expert does the required changes if it is essential and then the database is again locked.

**Coordination, monitoring and quality assurance.** The Maternal, Newborn, Child and Adolescent Health department (MCA) of the World Health Organization (WHO) is centrally coordinating the study. This involves technical input into the implementation as well as raising contracts with the constituent sites for the implementation. The WHO team has also procured the services of various experts from the United States of America, the University of Edinburgh in Scotland and Croatian National Biobank [31] to make specific input into various aspects of the study and to maintain the quality of implementation. Weekly (initially, but now fortnightly) teleconferences are held between team members from all the sites, the WHO team and the experts to discuss implementation challenges and to make decisions on the progress and strategies for the implementation. In preparation for these, sites present a progress report to the WHO which is discussed during the teleconferences. The experts are also commissioned at quarterly intervals to make visits to the sites to monitor the progress and quality of the implementation. After each visit, a detailed feedback is provided to the site and a report is also submitted to the MCA. In between site visits, the experts conduct videoconferences with the sites to monitor implementation. Other monitoring processes have been described in the other AMANHI publications [26,27].

**Ethical considerations.** The biomarker study has received ethical approval from the local and institutional ethics committees of all the three sites: ICDDR,B and John Hopkins University for Bangladesh, Aga Khan University for Pakistan and ZAMREC and John Hopkins University for Tanzania. The protocols were also approved by the WHO Ethics Review Committee and continuing approvals are obtained each new year. There will be no direct benefits of the study to the participants. They will be compensated for the time contribution to the sample collection at the health facilities.

**Plan for analyses.** Analyses of the epidemiological data will be carried out to characterize the women in the study and to link the various reported and measured exposures to the main outcomes. These will include principal components analyses (PCA) at each site to generate asset indices from the inventory of assets collected. These indices will be ranked and divided into quintiles and individual women will be assigned the wealth quintiles for their household. Associations will be explored using simple cross tabulations and tested with either a χ^2^ or Fisher exact tests for their significance. Where applicable, models with robust standard errors will be fitted to explore relationships. Multivariable regression models will be fitted in the risk factors analyses and likelihood ratio tests used to assess statistical significance.

**STEP 1: Testing existing hypotheses**. Simple, highly focused analyses to identify current hypothesized biomarkers associated with the risk of the main outcomes will be conducted using small aliquots of the biological samples. The analyses will seek to:

1. replicate the role of previously identified genetic variants which have been identified as important determinants of these outcomes in high income countries (HICs) through genome–wide association and candidate gene approaches and explore a panel of candidate genetic variants;

2. evaluate the validity of the most commonly proposed existing biochemical markers (in serum, plasma or urine) of these outcomes.

**STEP 2: Exploratory “hypotheses free” research using the biobanks**. Using high throughput “hypothesis free” approaches will be done to advance the science of biomarker–disease pathway discovery. This will include analyses of data from whole–genome arrays, high throughput data on many “–omics” traits, relevant maternal and newborn health outcomes and disease phenotypes. These will be “data driven” analyses in which novel high throughput technologies will be employed to yield high dimensional genomic, proteomic, lipidomic, glycomic and epigenetic data on large sample sizes to discover and identify entirely new associations and biomarkers. These analyses will require substantial financial investment and will be conducted through collaborations with other experts within countries and around the globe.

**Plan for dissemination of findings.** The results of the AMANHI biomarker study will be disseminated among the public health and maternal and newborn health community of researchers, policy–makers and programme managers. Channels for dissemination will include peer–reviewed journals, print and electronic media and through oral and poster presentations at appropriate fora. In each participating country, there will be extensive briefing on their country–specific and overall study results with interpretation of the potential implications for health programmes to the country.

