The key desirable attributes of such studies are clear aims and objectives, cultural and social acceptability to both participants and staff involved and low attrition rates. AMANHI has all these attributes. The harmonized implementation including the use of uniform protocols, centralised procurement of equipment, materials and reagents and the strict and rigorous quality control measures will allow for comparability of data across all sites which will allow for pooling and consequent use in the analyses of rare outcomes. A significant limitation of the AMANHI bio–repository study is its inability to inform on biological mechanisms underlying childhood linear growth and neurodevelopment. With the best characterized population based cohort in these LMICs, following up children into the 2nd and 3rd years after birth would have provided opportunities to examine epigenetic factors in pregnancy or early childhood that predict stunting and impaired neurodevelopment, the origins and risk factors of susceptibility to infectious agents and non–communicable diseases.

Establishing these biobanks is only the first step and will be of little value of it is not utilized to address current global challenges. Strategic investment to maximise the utility and gains from this infrastructure is an ethical call. This investment will allow for the use of existing and newly developed ultra–high throughput technologies and develop local capacity to participate and use such technologies to address global health challenges.

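### Crude cross-tabulations are named and pooling of three countries is relied on, but site is not a stratum, covariate or matching factor in any association analysis, so pooled tests can be confounded by site

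*Protocol article*

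**What the plan says.** All from the protocol article.

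- **Plan for analyses, first paragraph.** Its scope is set at the start: "Analyses of the epidemiological data will be carried out to characterize the women in the study" and to relate reported and measured exposures to the main outcomes. The univariate method follows: "Associations will be explored using simple cross tabulations and tested" with χ² or Fisher exact tests. Two further methods are given. Where applicable, "models with robust standard errors will be fitted to explore relationships". Then: "Multivariable regression models will be fitted in the risk factors analyses and likelihood ratio tests used to assess statistical significance". No covariates are listed and site is not mentioned for any of these. The one analysis specified by site is "principal components analyses (PCA) at each site to generate asset indices".
- **Plan for analyses, STEP 1.** Previously reported variants are to be replicated through "genome–wide association and candidate gene approaches and explore a panel of candidate genetic variants", and existing biochemical markers evaluated. No test, stratum or ancestry control is named. STEP 2 names none either.
- **Sample size considerations.** There are 1000 women at each of three sites, one pre-eclampsia prevalence of 3%, and a case-control design with three controls per case. Selection of controls within site is not mentioned.
- **Discussion.** Harmonised procedures make data comparable across sites, "which will allow for pooling and consequent use in the analyses of rare outcomes".
- **Plan for dissemination of findings.** Results are to be presented for each country as well as overall.

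**The concern.** The sites are Sylhet, Karachi and Pemba Island, on two continents. The article describes further differences. The Karachi communities are peri-urban, the intervals between pregnancy-surveillance visits differ, and field laboratories with shuttle freezers are used at Karachi and Pemba only. Harmonised protocols deal with measurement. They do not equalise ancestry, exposure patterns or baseline risk.

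If an outcome is commoner at one site and an exposure or marker is also commoner there, cases in the pooled table come disproportionately from that site and carry its exposure frequency. A χ² or Fisher test on that table then responds to site, not to the exposure. Robust standard errors do not help: they change the variance and leave the estimate confounded. A wealth index built by site does not adjust for site either. At stake are the false-positive rate and the odds ratios of the pooled analyses. Pooling cannot easily be avoided, since 3% of 1000 is only about 30 pre-eclampsia cases per site.

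**Working it through.** The article gives no figure on this point to reproduce. Its power statement is a separate matter and is not used here.

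**Inputs from the article.** Three sites of 1000 women; 3% pre-eclampsia, so 0.03 × 3000 = 90 cases; 1:3 ratio, so 270 controls; 5% significance (two-sided assumed).

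**Assumed inputs.** Site-specific outcome risks r and exposure frequencies e. The article gives neither, so a range is shown. There is no effect within any site.

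**Step 1: exposure frequencies in the pooled table.** Controls are drawn from all non-cases regardless of site.

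- Cases: p1 = Σ(r·e) / Σr
- Controls: p0 = Σ((1−r)·e) / Σ(1−r)
- Crude OR = [p1/(1−p1)] / [p0/(1−p0)]

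Example with risks 2/3/4% and exposure 10/30/50%:

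- p1 = (20×0.1 + 30×0.3 + 40×0.5)/90 = 31/90 = 0.3444
- p0 = (980×0.1 + 970×0.3 + 960×0.5)/2910 = 869/2910 = 0.2986
- OR = 0.5254/0.4258 = 1.23, although the OR is 1 at every site

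**Step 2: rejection rate of the crude test.**

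- Pooled proportion: (31 + 270×0.2986)/360 = 0.3101
- SE under the null: √[0.3101×0.6899×(1/90 + 1/270)] = 0.0563
- SE at p1, p0: √[0.3444×0.6556/90 + 0.2986×0.7014/270] = 0.0573
- Rejection rate: Φ[(0.0458 − 1.96×0.0563)/0.0573] + Φ[(−0.0458 − 1.96×0.0563)/0.0573] = 0.130 + 0.003 = 13%

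**Step 3: range, 90 cases and 270 controls.** A noncentral χ² calculation gives the same rates to within about 1.5 percentage points.

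| Outcome risk by site | Exposure by site | Crude OR | False-positive rate |
|---|---|---|---|
| 3/3/3% | 10/30/50% | 1.00 | 5.0% |
| 2/3/4% | 25/30/35% | 1.06 | about 5.5% |
| 3/4/2% | 10/30/50% | 0.90 | 6.7% |
| 2.5/3/3.5% | 10/30/50% | 1.11 | 7% |
| 2/3/4% | 10/30/50% | 1.23 | 13% |
| 2/2/5% | 10/30/50% | 1.36 | 24% |
| 1.5/3/4.5% | 10/15/50% | 1.41 | 25% |
| 1.5/3/4.5% | 50/15/10% | 0.67 | 25% to 27% |

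Equal risk at all sites, or equal exposure at all sites, gives OR 1.00 and 5%. If an allele-count test were used (180 and 540 alleles; the article names no genetic test), exposure 10/30/50% would give 9%, 21% and 41% for risks 2.5/3/3.5%, 2/3/4% and 2/2/5%.

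**Step 4: a commoner outcome, all 3000 women, assumed risks 20/30/40%.**

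- Exposure 10/30/50%: p1 = 310/900 = 0.3444, p0 = 590/2100 = 0.2810, OR 1.34, rejection rate 93%.
- Exposure 25/30/35%: p1 = 280/900 = 0.3111, p0 = 620/2100 = 0.2952, OR 1.08, rejection rate 14%.

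**Step 5: the remedy under the same assumptions.** With three controls per case at each site, controls have the same site mix as cases. Then p0 = p1, the crude OR is 1.00, and the rate is about 5% in every scenario. A site-stratified test reaches the same result through the analysis, since each stratum has OR 1.

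**The case against.** **The χ²/Fisher sentence is about epidemiological data.** A reader might infer that biomarkers and genes will be tested by crude tables. The article does not say so: that sentence concerns exploration of the epidemiological data, and STEP 1 and STEP 2 name no test. This limits what the point can claim for markers. It does not clear the exposure analyses, to which the sentence applies directly.

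**Adjusted models are planned.** Multivariable regression follows in the same paragraph and could include site, and controls could be matched by site. No sentence says that site will be ignored, and a stratified analysis is also a form of pooling. Promised results by country suggest that site will be looked at. All of this is fair. Still, nothing in the text commits the association analyses or the control selection to using site.

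**This is a condensed article.** Covariate lists and matching factors are commonly left to a full protocol or analysis plan, so their absence alone is no fault. That is right. The point rests instead on what the article does fix: a crude test as the named univariate method, together with reliance on pooled data.

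**The illustrations are chosen.** A reader might also infer that false associations will appear. The documents give one prevalence and no site-specific risks, exposures or allele frequencies. The Discussion's remark on systematic exposure differences follows a contrast between high-income and developing countries, not between these three sites. Bias requires risk and exposure both to differ by site, and several rows of the table show little or none. The shuttle-freezer difference is described as minor, with logged temperatures, and carries little weight here.

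**Conclusion.** The point holds in limited form. The article names crude tests for the epidemiological associations and depends on pooling three sites, while site enters no stated association analysis or control selection. Crude pooled tests can therefore show associations that exist in no site.

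The size depends on site values that the article does not give. With 90 cases and 270 controls, the false-positive rate runs from about 5% to 7% for mild or unaligned differences to about 25% for strong gradients, with crude ORs from 0.67 to 1.41. With a common outcome in all 3000 women, modest exposure differences already give 14% and strong ones 93%. These figures assume no effect within any site, no adjustment and controls drawn without regard to site. They show what is possible and do not predict what will happen. The change should be made because the better method is nearly free and uses a variable already held for every woman.

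**What to change.** 1. Replace the crude pooled χ² and Fisher tests with site-stratified tests: Mantel-Haenszel, or exact stratified tests where counts are small.
2. Include site in every pooled regression, as a covariate or as strata.
3. Select the three controls per case within site, and keep site in the analysis as well.
4. Report site-specific estimates and a test of heterogeneity across sites. With about 30 pre-eclampsia cases per site that test will be weak, so the estimates and their intervals matter more.
5. For genetic variants, state that analyses are done within site and then combined, with ancestry principal components where array data exist.

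Items 1, 2 and 4 are wording changes that cost a few degrees of freedom. Item 3 constrains the design and must be settled before stored samples are drawn for assay. The ancestry components in item 5 depend on the whole-genome arrays, which the article places under STEP 2 and says will need substantial funding; within-site analysis does not depend on them.

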## DISCUSSION

We present here the protocols used for the harmonised implementation of, to the best of our knowledge, the first population–based harmonized multi–country bio–repository study to be set up in developing country settings. With data on phenotypic and epidemiological characteristics and most importantly epigenetic and biochemical information, this study may have the best characterized cohort of pregnant women and their newborns in the entire developing world; certainly so in south Asia and sub–Saharan Africa. Successful implementation of the study affords the opportunity to explore hypothesized risk factors for adverse pregnancy outcomes and also allow further explorations into biomarker–disease pathway along several dimensions in LMICs.

Hitherto, biobanking has largely been the preserve of developed country settings [19,20]. There is however a systematic challenge in translating research results from such settings to developing country settings. Also whilst non–communicable diseases tend to be the main agenda for biobanks in HICs and hence a lot of emphasis is on adult health outcomes, infectious diseases as well as preventable maternal, newborn and child deaths will require much greater focus in developing country settings [20]. There are also systematic differences in exposures to various risk factors due to differences in culture, workplace environment, lifestyle and access to health care. In contrast to HICs, vital registration systems are non–existent in LMICs, health systems are weak and majority of the population do not have access to health services and hence a facility–based bio–repository will have significant biases and may not be representative. It is believed that when biobanks are sited in LMICs, they will likely address specific needs and equity considerations [20,32,33].

A review by McKinnon et al [7] on birth cohort studies in South East Asia and Eastern Mediterranean found only few studies that saved biological samples. Most of these studies had small sample sizes and were of relatively low quality. Only one of the studies had DNA samples stored for later analyses and none took genetic material from family members. Other logistical challenges such as availability of reliable power supply, the ability to assemble sufficient human resource with the capability of setting up such biobanks in LMICs are often thought of as reasons why such biobanks will not be feasible in LMICs [25] which carry over 95% of the world’s burden of morbidity and mortality around childbirth [34].

The AMANHI study proves the principle that such biobanks are feasible to set up in developing country settings. The AMANHI sites are collecting population level data that is very representative of rural populations is the study settings. The inclusion of genetic material and data from family members that can be used directly or “as proxies of exposure” for the identification of “parent–to–origin effects and de novo mutations” is quite novel in these developing country settings. It will therefore contribute to knowledge in the testing of existing hypothesis around risk factors for adverse pregnancy and birth outcomes in these LMICs of sub–Saharan Africa and south Asia who carry the highest burden of these. It will establish a platform for further exploration of new hypotheses and technologies and build local capacity in these low–resource settings for high quality research and ultra–high throughput analyses. Its analytical approach including “hypothesis–free” analyses has been described as one that is potentially free of human biases and may create opportunities for breakthrough discoveries in the biomarker–disease pathways [19]. Its implementation provides a model for adaptation in conducting high impact research in similar settings.

The key desirable attributes of such studies are clear aims and objectives, cultural and social acceptability to both participants and staff involved and low attrition rates. AMANHI has all these attributes. The harmonized implementation including the use of uniform protocols, centralised procurement of equipment, materials and reagents and the strict and rigorous quality control measures will allow for comparability of data across all sites which will allow for pooling and consequent use in the analyses of rare outcomes. A significant limitation of the AMANHI bio–repository study is its inability to inform on biological mechanisms underlying childhood linear growth and neurodevelopment. With the best characterized population based cohort in these LMICs, following up children into the 2nd and 3rd years after birth would have provided opportunities to examine epigenetic factors in pregnancy or early childhood that predict stunting and impaired neurodevelopment, the origins and risk factors of susceptibility to infectious agents and non–communicable diseases.

Establishing these biobanks is only the first step and will be of little value of it is not utilized to address current global challenges. Strategic investment to maximise the utility and gains from this infrastructure is an ethical call. This investment will allow for the use of existing and newly developed ultra–high throughput technologies and develop local capacity to participate and use such technologies to address global health challenges.
